**1. Background**

SARS-CoV-2 vaccination was introduced in the UK on 7th December 2020. Initial clinical trial results and population studies on vaccine effectiveness (VE) showed that the vaccines were successful in preventing infection, but population studies suggest that this has lessened with antigenic change in the virus over time, though effectiveness against severe outcomes remains moderate. Continued monitoring in the wider population is important to optimize vaccination strategy to minimize the burden of disease. A large GP data source will help detect differences in VE between clinical groups.

Strong systems to evaluate the effectiveness of the COVID-19 vaccine programme will enable to:

- optimise recommendations for the use of the vaccine
- target complementary or alternative public health measures (e.g. antivirals) for population segments where vaccine is less effective.
- allow more precise estimates of the impact of current vaccination strategies on the burden of disease to support the national vaccination campaign
- evaluate COVID-19 vaccines to better understand optimal composition; use of adjuvants; need for booster doses.
- better manage and respond to reports of vaccine failures.
- counterbalance the reports of adverse events following immunisation by providing elements for an adequate risk management and cost-effectiveness analysis.

This proposal concerns the use of the established general practice database maintained by the Oxford-Royal College of General Practitioners (RCGP) Research and Surveillance Centre (RSC), one of Europe’s oldest sentinel systems.^[[1]](#footnote-1)^ The RCGP RSC has supported and collaborated with Public Health England and predecessor bodies for over 50 years and adapted significantly to meet the challenges of the pandemic.^[[2]](#footnote-2),^^[[3]](#footnote-3)^

We will use cohort and case-control methods to estimate COVID-19 VE against a range of clinical and virological endpoints, with a focus on the 2022 Autumn, 2023 Spring and 2023 Autumn booster programmes.

We propose the dataset for analysis aims to include:

1] The inclusion of results of laboratory tests via both Pillar testing and Sentinel surveillance, both historical and current.

2] Information on the type and dose of vaccine given, manufacturer and batch number.

3] Patient specific information on demographic variables, risk group status and prior influenza vaccine history.

4] Further linked relevant outcome data, in particular hospital admission and mortality data.

**2. Objectives**

**2.1 Aim**

For the 2023/24 period, the aims are to:

- Describe the population that have received a booster vaccine at the time of data extraction.
- Estimate COVID-19 vaccine effectiveness for a range of clinical and virologically confirmed end-points in primary care across all age groups.

**2.2 Primary objectives**

The key questions to be addressed for confirmed COVID-19 infection and clinical outcomes in 2023/24 in relation to vaccine effectiveness, taking into account previous vaccination and booster vaccination, will be to estimate:

- Overall VE by vaccine type (mRNA or other)
- VE by specific clinical risk group
- VE by time since vaccination
- VE by time period, depending on the timing of boosters and circulation of specific variants

| Outcomes combine confirmed and clinical elements:  **Confirmed**: Swab either taken   - via GP from persons presenting with COVID-like symptoms. Laboratory investigation undertaken in the PHE Respiratory Virus Reference laboratory to detect positive swab for SARS-CoV-2 and other respiratory viruses.   **Clinical:**   - COVID-19 coded hospitalisation - COVID-19 coded death - death within 28 days of positive SARS-CoV-2 test. |
| --- |

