**Ascertainment**

Vaccination status, date, manufacturer and type is extracted from the study database (and linked from other sources if necessary).

Individuals will contribute pre-booster person time up to the point of booster vaccination and thereafter assigned to categories based on combinations of time since dose and booster vaccination type

Time since dose:

- pre-booster/unboosted (baseline)
- 0-13 days,
- 14-91 days,
- 92-182 days,
- 183+ days

Type of vaccine:

- mRNA XBB
- mRNA bivalent original/BA.4-5
- recombinant Beta

These categories may be assigned separate factors for different manufacturers, as required.

The following are considered ‘odd’ vaccination histories, to be considered for exclusion:

- Other vaccine types than those listed in section 3.4 above
- Vaccination between 13 February and 3 April 2023 (for Spring 23 booster analysis)
- Vaccination between 31 June and 3 Sept 2023 (for Autumn 23 booster analysis)

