**Cohort study**

V/E is calculated as 1- RR, where RR is the attack rate of the vaccinated group over the attack rate of the unvaccinated group.

Multivariable Poisson regression will be used with vaccination and week set as time varying covariates and all other variables set according to the individual’s status as of 1^st^ September 2022 (or 2023).

Adjustment for week of swab, age group, sex, risk-status and region (or practice) and will be included at minimum. Inclusion of additional variables including consultation quartile, IMD quintile, ethnicity, smoking status, influenza vaccination status, EFI, large residence, Cambridge Mortality Measure, will be considered individually; variables that do not impact both hospitalisation or death VE by more than 1% need not be included (i.e. the same adjustments will be made for both death and hospitalisation VE).

Vaccination status will be a time-varying categorical variable: 0-13 days post dose, 14-90 days post dose, 91-182 days post dose, with separate categories for vaccine type (and manufacturer if required). Vaccinated 6months+ ago will be the baseline category, to look at the incremental benefit of a new dose.

Person time will be calculated in days and adjusted for as an offset in the model.

The reshape and collapse commands in Stata will be used to aggregate person time and events across the levels of the time varying and fixed covariates.

Cohort analyses will be carried out for both hospitalisation and death outcomes.

Primary cohort analysis will include complete cases only, but unknown categories may be included for some missing data items.

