**TND study**

V/E is calculated as 1-OR. Where OR is the odds of vaccination in cases compared to controls (SARS-CoV-2 negative).

Multivariable logistic regression will be used with adjustment for week of swab, age group, risk-status and region (or practice), at minimum. Inclusion of additional variables including sex, consultation quartile, ethnicity, IMD quintile, smoking status, EFI, large residence, Cambridge Morality Measure, and indication for swabbing (grouped as ILI / COVID-like illness, ARI or exacerbation) will be considered individually; variables that do not impact VE by more than 1% need not be included.

Vaccination status will be a categorical variable, captured at the time of swabbing: 0-13 days post dose, 14-91 days post dose, 92-182 days post dose, with separate categories for each vaccine type (or manufacturer if required). Vaccinated 6months+ ago will be the baseline category, to look at the incremental benefit of a new dose.

Primary TND analysis will impute onset status (within/beyond 10 days) where this is not given.

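### The primary COVID-19 objective promises to take previous vaccination into account, but no confounder list or named adjuster carries earlier COVID-19 doses, and the 6months+ baseline only partly fills the gap

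*Protocol*

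**What the plan says.** All references are to the COVID-19 study in the Protocol.

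- **Objective.** Section 2.2 says VE will be estimated "taking into account previous vaccination and booster vaccination".
- **Cohort model (3.12).** The required adjusters are: "Adjustment for week of swab, age group, sex, risk-status and region (or practice) and will be included at minimum". The further candidates, screened on a 1% change in VE, are named as "consultation quartile, IMD quintile, ethnicity, smoking status, influenza vaccination status, EFI, large residence, Cambridge Mortality Measure".
- **Test-negative (TND) model (3.12).** The required set is: "Multivariable logistic regression will be used with adjustment for week of swab, age group, risk-status and region (or practice), at minimum". The candidates include "sex, consultation quartile, ethnicity, IMD quintile, smoking status, EFI, large residence", a mortality measure and the indication for swabbing.
- **Confounders (3.8 and Table 1).** Influenza vaccination is listed. Earlier COVID-19 vaccination is not. Table 1 does collect all COVID-19 vaccinations with their dates and types, but as exposure data.
- **Reference group.** Both models state: "Vaccinated 6months+ ago will be the baseline category, to look at the incremental benefit of a new dose". Section 3.5 instead makes the reference "pre-booster/unboosted (baseline". The cohort VE formula says that "RR is the attack rate of the vaccinated group over the attack rate of the unvaccinated group".

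**The concern.** People who accept a new booster tend to be those who accepted earlier ones, and earlier doses can themselves affect the risk of infection, admission or death. Earlier dose history is thus a candidate confounder of the effect of the new dose. It is also the one that the primary objective singles out, yet it is missing where the Protocol names its adjusters.

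At stake is the incremental benefit that section 3.12 sets out to measure. If boosted and reference people differ in earlier doses within levels of age, risk status, region and week, part of the effect of those doses is attributed to the new one. Section 4.5 concedes that healthy-vaccinee bias will be hard to capture. Past uptake of COVID-19 vaccine is a marker of willingness to be vaccinated that the study already holds. Section 4.4 plans to allow for past infection where possible, but nothing comparable is planned for past doses.

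**Working it through.** The Protocol gives no figure to reproduce. The check has three parts.

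**1. Is dose history named anywhere as an adjuster?** Section 3.8, the confounder rows of Table 1, and the required and candidate lists for both models were compared. None names the number, type or timing of earlier COVID-19 doses. The only vaccination covariate is influenza vaccination, in 3.8, Table 1 and the cohort candidates.

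**2. Does the 6months+ baseline equalise histories?** Take the Spring 2023 evaluation and read six months as the 183+ day band in section 3.5.
- Inputs: the Autumn 2022 campaign ran 5 September 2022 to 12 February 2023 (3.4). The Spring analysis runs 3 April to 3 September 2023 (3.4).
- 3 April 2023 − 183 days = 2 October 2022. On day one the reference group contains only people last dosed on or before 2 October 2022: those who skipped the autumn dose, or who had it in the first four weeks of the campaign.
- 12 February 2023 + 183 days = 14 August 2023. The latest autumn recipients enter the reference group 20 days before the analysis ends.
- Spring recipients may have had their autumn dose at any time up to 12 February 2023.

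The two groups can therefore differ in number and timing of earlier doses, and the make-up of the reference group shifts during follow-up. Adjusting for week handles changing incidence; it does not balance dose history between the groups within a week. Under the other two reference groups, in 3.5 and in the cohort rate-ratio definition, there is no earlier-dose condition at all.

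**3. How large could the effect be?** All inputs here are assumptions; the documents supply none.

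*(a) Unequal histories in the two groups.* Let q be the share of the reference group with a thin or old dose history, q1 the share among boosted people, and r their relative risk. Then inflation = (1 − q + q·r) / (1 − q1 + q1·r), and observed VE = 1 − (1 − VE) / inflation. Take q1 = 0.05.

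| q | r | Inflation | True VE 50% reads | True VE 0% reads |
|---|---|---|---|---|
| 0.20 | 1.25 | 1.0500/1.0125 = 1.037 | 51.8% | 3.6% |
| 0.30 | 2.00 | 1.300/1.050 = 1.238 | 59.6% | 19.2% |
| 0.20 | 0.70 | 0.940/0.985 = 0.954 | 47.6% | −4.8% |
| 0.30 | 0.70 | 0.910/0.985 = 0.924 | 45.9% | −8.2% |

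The last two rows show that the sign depends wholly on whether r is above or below 1.

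*(b) People outside the 6months+ group mixed into the reference, for example the never vaccinated.* Let f be their share and k their risk relative to people vaccinated six months or more ago. Observed VE = 1 − (1 − VE) / ((1 − f) + f·k). With f = 0, or with k = 1, there is no bias from this source. With f from 5% to 20% and k from 0.7 to 2.0:
- true VE 30% reads between 1 − 0.70/0.94 = 25.5% and 1 − 0.70/1.20 = 41.7%;
- true VE 60% reads between 1 − 0.40/0.94 = 57.4% and 1 − 0.40/1.20 = 66.7%.

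**The case against.** The strongest reply is that the exposure coding is itself how previous vaccination is taken into account. Newly boosted people are compared with previously vaccinated people, recency is graded, and unusual histories are excluded or considered for exclusion. That stands in part: a reader who sees no dose-history covariate might infer that earlier vaccination is absent from the models altogether, and section 3.12 contradicts that. If the 6months+ baseline is enforced, the mixing in (b) disappears. It leaves (a), unequal histories among the previously vaccinated, untouched.

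Second, the lists are not closed. One set is a minimum, the other is introduced as including the named items, and covariate coding may sit in an analysis plan that is not shown. This is fair as to coding. But the Protocol chose to name its adjusters and a screening rule, and the one its primary objective calls for should not depend on an open-ended list.

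Third, direction. Section 4.4 describes an opposing path: people already infected may be less likely to vaccinate, which pulls VE down. If thin dose histories go with past infection, r could be below 1. This stands, and it rules out a claim of certain overstatement.

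Fourth, the illustration is crude. It ignores the other adjusters and the restriction to eligible groups, both of which may absorb some of the imbalance. This also stands.

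**Conclusion.** The point holds as a gap between the primary objective and the named adjustment sets, which the 6months+ baseline closes only in part. Booster VE may carry residual confounding by earlier doses. Upward bias is plausible, because uptake of successive doses tends to go together and earlier doses may still protect. The documents establish neither direction nor size, and the figures above (true 50% reading about 46% to 60%) only show what the assumed inputs would produce.

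Two stronger readings are not supported. A reader might infer that booster VE is overstated for certain; that needs r above 1, which no section supplies and section 4.4 gives reason to doubt. A reader might also infer that campaigns cannot be compared with one another. The reference group does change with campaign dates, so any bias could differ between campaigns, but nothing in the documents shows that it does so by an amount that prevents comparison.

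The change is worth making before analysis: the data are already collected and the gap concerns a primary objective. The three differing reference groups also need to be reconciled, but settling on one would not by itself balance dose history.

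**What to change.** In section 3.8, the confounder rows of Table 1 and both models in section 3.12:

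1. Add to the minimum adjusters the number of COVID-19 doses received before the evaluation start date (5 September 2022, 3 April 2023, and the Monday of the first week of the Autumn 2023 programme), as a categorical variable fixed at that date. Because the objective promises this adjustment, it should not depend on the 1% screen.
2. State one reference group across 3.5 and 3.12, and say how never-vaccinated people are handled in line with it: a separate level of the dose-number variable, or excluded.
3. Add time since the last pre-campaign dose, in bands, only where it does not duplicate the exposure categories. For someone not yet boosted, this time plus calendar week largely determines the time-since-dose category. On 3 April 2023 the reference group contains nobody last dosed within 183 days. The bands should therefore be chosen where boosted and reference people overlap, and the variable is undefined for the never vaccinated.

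The cost is modest. The variables can be derived from the vaccination dates already in Table 1. The collapsed person-time table becomes larger and the intervals slightly wider.

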**2.3 Secondary objectives**

Descriptive statistics

To describe Spring and Autumn 2023 booster vaccine uptake in the RCGP population by target groups and by demographic and clinical variables.

**3. Methods**

**3.1 Study designs**

For 2023/24 RCGP RSC and UKHSA in collaboration will use two main study designs to estimate COVID-19 vaccine effectiveness in England across all age groups, and in sub-populations for individuals registered with participating GPs in the RCGP RSC sentinel network. The primary designs to be used are as follows:

- Cohort study with primary outcomes hospitalisation and death.
- Test-negative design (TND) study on patients within the sentinel swabbing scheme.

This proposal covers both the cohort study and the TND study.

**3.2 Study population and data source**

| Study population to be included:  Cohort study: Approx. 18,800,000 registered persons in England. About 20% of the study population are ≥65 years.  Swab based TND study: Restricting to those consulting their GP with symptoms and swabbed via the sentinel scheme, available positive cases and negative controls will depend on current prevalence and swab rates.  Spring 2023 boosters, will restrict to: individuals aged 75+, immunosuppressed individuals aged 16+  Autumn 2022/2023 boosters, will restrict to: individuals aged 50-74, individuals aged 75+, individuals aged 16+ in clinical risk groups |
| --- |

**3.2.1 Cohort study population**

***Definition***

The cohort study population is composed of the entire registered population in the participating practices in England. This will be those registered on or before the start of vaccine booster rollout.

The data capture methods include the collection of all relevant potential confounding variables (e.g. variables that may be associated with eligibility for vaccination and the outcome of interest) and information on vaccine type.

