**Exclusion criteria**

Registered patients will be excluded from the data extract if they have expressed a wish to be excluded from the surveillance programme.

Logical checks will be performed and patients identified with nonsensical records will be excluded. Those with unusual COVID-19 vaccine histories will be excluded.

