**3.4 Study period**

This proposal relates to an ongoing programme of disease surveillance. Data are collected continuously on a daily basis in England. It includes the diagnoses or problems reported at every consultation. The database can be interrogated in relation to any specific disease or in any defined period. It is assumed that the period of COVID-19 activity will continue throughout 2023 and 2024, this will be monitored through surveillance.

Autumn 2022 booster vaccine doses were offered to all age 50+ plus all members of clinical risk groups age 5+ and health and social care workers, carers or close contacts of the immunosuppressed. Autumn booster doses primarily included bivalent Original/Omicron BA.1 mRNA vaccines (Pfizer-BioNTech, Comirnaty or Moderna, Spikevax). The autumn booster vaccination campaign opened 5 September 2022 and closed 12 February 2023.

Spring 2023 boosters were offered to those age 75+ or those with weakened immune systems, during the period 3 April – 30 June 2023. Vaccines given were primarily either bivalent Original/Omicron BA.4-5 mRNA vaccines (Pfizer-BioNTech, Comirnaty) or monovalent Beta recombinant vaccines (Sanofi-GSK, VidPrevTyn).

From Autumn 2023, a new booster vaccine dose will be offered to all age 50+ plus all members of clinical risk groups age 5+ and health and social care workers, carers or close contacts of the immunosuppressed. Autumn booster doses will include monovalent XBB mRNA vaccines, bivalent Original/Omicron BA.4-5 mRNA vaccines, and monovalent Beta recombinant vaccines, depending on age and availability. The autumn booster vaccination campaign will be ongoing from September 2023.

The data may be examined in any arbitrary period according to interest. At the time of writing, Omicron XBB lineages are dominant, but this could change at any time, and variant may impact vaccine effectiveness. Study periods may be amended to cover variant-dominant periods of infection or according to decision makers needs. Cohort analyses may require censoring at the last date in records where outcomes appear to be well captured.

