**Propensity to consult**

- Number of consultations per patient for outcomes in previous year (e.g. Sep 2021-Aug 2022)
- Will be used to create age-standardised quartiles of consultation and a non-consulters group

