|  | Influenza vaccination | Electronic GP record |

The absence of any of those characteristics in the database is assumed to indicate no presence of the characteristic under study (missing values are coded absent).

Covariate values are updated on 1^st^ September of each study year on information recorded in the study database.

| Continuous update of co-variates takes place. However, some need to be defined pre-season for analysis. |
| --- |

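### Cohort entry by list registration alone does not fit the 12-month covariate window, and it leaves unlinked leavers in the unboosted reference group and the uptake denominator

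*Protocol*

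**What the plan says.** All references are to the COVID-19 study in the protocol.

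- **Entry (3.2.1, Definition).** "The cohort study population is composed of the entire registered population in the participating practices in England". The only time condition is: "This will be those registered on or before the start of vaccine booster rollout".
- **Exclusions (3.2.1).** "Registered patients will be excluded from the data extract if they have expressed a wish to be excluded from the surveillance programme". In addition, "Logical checks will be performed and patients identified with nonsensical records will be excluded", and unusual COVID-19 vaccine histories are removed.
- **Exit.** The one censoring statement for the cohort, in 3.4, concerns data completeness: "Cohort analyses may require censoring at the last date in records where outcomes appear to be well captured". Leaving the list or the country is not mentioned.
- **Person-time (3.5).** A person adds pre-booster time until a booster is recorded.
- **Consultation covariate (3.8).** Consultations are counted over the previous year, with September 2021 to August 2022 as the example. The count is then grouped: "Will be used to create age-standardised quartiles of consultation and a non-consulters group".
- **Absent data (3.9, below Table 1).** "The absence of any of those characteristics in the database is assumed to indicate no presence of the characteristic under study".
- **Model (3.12).** Risk status is always adjusted for. Consultation quartile is one of the candidates that may be left out if it moves VE by no more than 1%.
- **Uptake (2.3).** "To describe Spring and Autumn 2023 booster vaccine uptake in the RCGP population by target groups", and by demographic and clinical variables.

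**The concern.** The entry rule and the covariate rules do not fit together. A person who registered shortly before rollout is eligible, but the consultation count needs a full prior year and the risk flags need a history. If the earlier record is not in the extract, the count is too low and risk conditions are read as absent. The complete-case provision in 3.12 does not catch this, because a zero count and a negative flag are not missing values. These covariates are the means by which the plan controls health-status confounding.

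The second problem is people who remain listed but are no longer present. If neither a booster nor an outcome can reach their record, they stay unboosted and event-free for the whole follow-up. That lowers the reference rate and therefore VE. They also count in the denominator of the uptake tables, where no model adjustment applies.

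Other parts of the document are stricter. The COVID-19 test-negative study excludes people without a linked vaccination history or clinical risk status. The influenza study restricts residence and drops English patients with neither a NIMS nor a GP link. The cohort is the design in which list membership alone creates person-time, and it has no comparable check. The limitations in section 4 do not mention list inflation.

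**Working it through.** **The plan's own figures.** The protocol gives no share of recent registrants or departed patients, and no coverage. Its only cohort figure is the 1% attack rate in 3.10. Reading 15 per 10,000 as a weekly rate, 0.0015 × 6 = 0.90% and 0.0015 × 7 = 1.05%, so the 1% reproduces. It concerns precision and says nothing about this bias. All inputs below are therefore assumptions.

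**1. Dates.** Covariates are fixed at 1 September 2022 (or 2023). The Autumn 2022 analysis starts on 5 September 2022, so anyone who registered after about 1 September 2021 has less than the required window at that practice. The Spring 2023 analysis starts on 3 April 2023. If its covariates are those of 1 September 2022, a person who registered between the two dates has no time at that practice in the window at all.

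**2. Miscoding among recent registrants.** Assume registration dates spread evenly over the prior year, r consultations per year (Poisson) and no transferred history. The share coded non-consulting is (1 − e^−r)/r; the true share is e^−r.

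- r = 5: 0.199 coded against 0.007 true.
- r = 2: 0.432 coded against 0.135 true.

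These are shares of recent registrants, not of the cohort.

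**3. Effect of miscoding on VE.** A Poisson model with person-time offset was fitted to expected counts. Assumptions: true VE 60%; 30% of people at high risk with rate ratio 3; coverage 80% in high-risk and 50% in low-risk people; a share h of the list coded low-risk regardless of true status.

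| h | registrants' coverage as others' | their coverage 50% | their coverage 30% |
|---|---|---|---|
| 2% | 59.6% | 60.0% | 60.3% |
| 5% | 59.0% | 60.0% | 60.6% |
| 10% | 58.1% | 60.0% | 61.1% |

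The shift is at most 1.9 points, and its sign changes with the registrants' coverage.

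**4. Unlinked leavers, crude VE.** Let g be their share of the list and c the true coverage of those present. All leavers sit in the reference group with no events:

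observed RR = true RR × [(1 − c)(1 − g) + g] / [(1 − c)(1 − g)].

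For c = 80%, g = 2%: (0.196 + 0.02)/0.196 = 1.102, so VE = 1 − 0.4 × 1.102 = 55.9%. With true VE 60%:

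| c | g = 1% | g = 2% | g = 5% |
|---|---|---|---|
| 50% | 59.2% | 58.4% | 55.8% |
| 65% | 58.8% | 57.7% | 54.0% |
| 80% | 58.0% | 55.9% | 49.5% |
| 90% | 56.0% | 51.8% | 38.9% |

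**5. The same with a non-consulters term.** Assume genuine non-consulters are 15% of those present, have 0.4 times the event rate of others, and share their stratum with all the leavers.

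| c | g | genuine non-consulters' coverage as others' | their coverage 40% |
|---|---|---|---|
| 65% | 2% | 59.2% | 59.6% |
| 65% | 5% | 58.3% | 59.1% |
| 80% | 2% | 58.6% | 59.5% |
| 80% | 5% | 57.1% | 58.9% |

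The loss falls to 0.4 to 2.9 points.

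**6. Uptake.** Observed uptake = c(1 − g). True 80% reads as 0.80 × 0.98 = 78.4%, or 0.80 × 0.95 = 76.0%.

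**The case against.** The strongest reply is that outcomes do not depend on the practice record. Sections 3.6 and 3.9 link to SGSS, SUS/HES and ONS mortality, and Table 1 names NIMS as a vaccination source. A listed person who moved within England can still have an event, and with NIMS a booster, captured. This stands. A reader might infer that every departed patient is event-free and unboosted; the document does not support that. The event-free route applies mainly to people who left England or cannot be linked. However, 3.5 makes outside vaccination linkage conditional. Without it, boosted movers count as unboosted while their events are kept, which is a different error from the same gap.

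Three further points reduce the size.

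- Section 3.12 takes people vaccinated six or more months ago as the baseline, which removes never-vaccinated leavers but not those with an old dose. Section 3.5 names the unboosted as baseline, which removes neither. The two sections need reconciling.
- If leavers moved VE by several points, the consultation variable would be expected to pass the 1% rule and stay in the model. That is likely, but not fixed in advance, and it does nothing for the uptake tables.
- Vaccination is time-varying and week is adjusted for. Everyone starts unboosted, so leavers are a small part of the reference group early on. The formula in step 4 holds coverage constant and overstates the effect over a whole campaign.

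Two more readings go too far. One is that recent registrants bias VE in a known direction: step 3 shows otherwise, and section 3.3 describes practice databases as accumulated records, so some history may transfer. The other is that age-group comparisons are distorted most at 75+. That needs the leaver share to be no lower at those ages, and nothing in the document says so.

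Whole-list entry with a consultation covariate is a legitimate design, and a sensitivity run could sit in an analysis plan not shown here. But the eligibility definition is stated here, and it conflicts with the covariate window stated here.

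**Conclusion.** The mismatch between the entry rule and the 12-month covariate window is real and should be corrected. Its effect on VE is probably small (within about 2 points in the cases run) and of either sign. Unlinked leavers lower VE and reported uptake. The direction is clear, but the protocol does not allow the amount to be derived.

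The crude losses of 0.8 to 21 points in step 4 should not be read as the expected bias. They assume 1% to 5% unlinked leavers, coverage of 50% to 90%, all leavers in the reference group, constant coverage and no adjustment. With the non-consulters level in the model the loss was 0.4 to 2.9 points, and the 3.12 baseline and national linkage would reduce it further. Care is also needed with the unboosted share if the formula is written as 1 − (1 − VE)/(1 − g/u). Here u includes the leavers, so 80% true uptake with g = 5% gives u = 0.20 × 0.95 + 0.05 = 24%. At true VE 50% that yields 36.8%, not the 33.3% obtained with u = 20%.

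**What to change.** 1. In 3.2.1, require 12 months' registration before the covariate date, or admit shorter registrations and give them their own covariate level.
2. In 3.12, keep the consultation/non-consulters term in the cohort model rather than leaving it to the 1% rule.
3. In 3.5, use NIMS linkage for vaccination status throughout, not only where judged necessary.
4. Beside the full-list result, report one sensitivity run of the cohort models and uptake tables restricted to people with evidence of presence in the 12 months before entry: a consultation, prescription or other contact. COVID-19 vaccination alone should not count. A looser filter would fail. UK vaccination began on 7 December 2020 and the Autumn 2022 analysis starts on 5 September 2022, so with a 24-month window that accepted a dose, every earlier dose would qualify and leavers with an old dose would stay in.

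The cost is a filter on registration date and activity in the GP record, plus one re-run. Some recent registrants and genuine healthy non-attenders drop out of the restricted analyses. Selecting on contact has its own bias, so the presence restriction should remain a sensitivity analysis.
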